# Family-based improvement for health literacy among the Yi nationality (FAMILY) in Liangshan: protocol of an open cohort stepped wedge cluster randomized controlled trial

**DOI:** 10.1186/s12889-022-13782-w

**Published:** 2022-08-13

**Keywords:** Health literacy, Family branch system, Contracted family doctor services, Stepped wedge cluster randomized trial, Mixed-effects model, Complier average causal effects

## Abstract

**Background:**

Improvement of health literacy constitutes a cornerstone to improving public health. However, the overall health literacy of Liangshan Yi Autonomous Prefecture (Liangshan Prefecture) in the southwest Sichuan Province of China has kept extremely low for a long time. How to improve health literacy of the Yi nationality residents is key to be urgently solved. Notably, Family Branch System is a distinctive patrilineal bloodline organization of Yi nationality, which plays an important role in the daily life of Yi nationality. Meanwhile, Contracted Family Doctor Services is conducted in Liangshan Prefecture. Therefore, this study proposes an intervention model of health education based on Family Branch System and Contracted Family Doctor Services, which is a Family-based Improvement for Health Literacy among the Yi nationality (FAMILY) in Liangshan, when improving traditional Innovative Care for Chronic Conditions Framework (ICCC) framework.

**Methods:**

An open cohort stepped wedge cluster randomized trial design is used to implement health literacy education interventions including project preparation, core group building, promotion within family branch and competition between family branches while using Contracted Family Doctor Services as control measure. The study will be conducted among Yi nationality residents in Meigu County and Yanyuan County, with health literacy level of residents as the primary outcome. Finally, mixed-effects model and causal inference method will be used to evaluate intervention effect.

**Discussion:**

This study highlights family, using the unique Family Branch System and Contracted Family Doctor Services in Liangshan Prefecture to design intervention among improved ICCC framework, and combines the mixed-effects model with complier average causal effects (CACE) to estimate the intervention effect under non-compliance for the first time. Besides, other key technologies to be adopted include construction of electronic questionnaire quality control system, with quality control based on artificial intelligence. This trial contributes to exploring an effective way to improve health literacy of Yi nationality residents in Liangshan Prefecture, which will provide reference for other areas, especially poor areas, to improve residents’ health literacy.

**Trial registration:**

ISRCTN11299863 on June 1, 2022; https://www.isrctn.com/.

**Supplementary Information:**

The online version contains supplementary material available at 10.1186/s12889-022-13782-w.

## Background

Improvement of health literacy constitutes a cornerstone to improving public health [1, 2]. It is an important strategy and measure to improve people’s health, an important part of promoting constructing Healthy China, and one of the main indicators in the *Outline of the Healthy China 2030 Plan* [3]. However, under influence of economic development and historical changes, the health literacy level of residents in Liangshan Yi Autonomous Prefecture (Liangshan Prefecture), where located in the southwest Sichuan Province of China, is still at a low level (only 11.62%). This level is lower than that of Sichuan province in 2019 (19.40%) and rural residents in 2017 (14.5%), indicating a big gap between the overall requirement of the *Outline of the Healthy China 2030 Plan* [3] still exists. In addition, the health literacy level of residents in some Yi autonomous counties are even only about 1% [4]. Therefore, how to improve the health literacy of the Yi nationality residents is a key issue to be urgently solved in the realization of *the Outline of the Healthy China 2030 Plan* in Liangshan Prefecture.

International scholars have conducted in-depth research on how to improve the prevention and management of Noncommunicable diseases (NCDs). Among many proposed models and theories, Chronic Care Model (CCM) and Innovative Care for Chronic Conditions Framework (ICCC) have been widely recognized and applied [5]. Compared with CCM, ICCC framework is more specific, operational, and suitable for low- and middle- income regions. The ICCC framework elucidates that individuals and their families are an undervalued asset in health care system, which emphasizes the role of individuals and families, and the need to promote them to partner with communities and health care organizations [6, 7]. Positive outcomes in NCDs management can only be achieved when individuals, family, community partners and healthcare working groups are informed, motivated, prepared and work together [8].

As mentioned above, family could make an important contribution to health promotion. Thus, in the process of improving the Yi nationality residents’ health literacy in Liangshan Prefecture, we should fully respect the local ethnic customs and habits, and also give full play to the role of family, which could be achieved through Family Branch System and Contracted Family Doctor Services. Yi nationality is a mountainous nation, many of whom live in the mountains with relatively backward traffic, making them have little contact with the outside and less influenced by foreign culture [9, 10]. Its traditional culture has a greater influence on the social life and play an important role in the process of social development. Notably, Family Branch System is a distinctive patrilineal bloodline organization of Yi nationality in ancient times [11], which has been passed down to this day and plays a vital part in the daily life of Yi nationality. A large number of practical experiences show that during the transition from slave society to socialist society in Liangshan Prefecture, Family Branch System has exerted a significant influence on drug control, grass-roots governance and legal construction [12]. For example, at the end of 2017, the National Health Council and Sichuan Provincial People’s Government jointly launched and implemented the AIDS prevention, treatment and health poverty alleviation campaign in Liangshan Prefecture [13]. In the special implementation process of management capacity building, Liangshan Prefecture has carried out pilot work in its Meigu County and Yanyuan County in response to the problems exposed in grass-roots PMTCT management [14], expanded the scope of capacity building from business and service support to comprehensive management, and fully utilized the key personage of the family branch. In addition, many foreign studies also showed that in less developed countries and regions such as sub-Saharan Africa, tribal culture similar to the family branch system was also critical in environmental protection and HIV prevention and control [15, 16]. Meanwhile, Contracted Family Doctor Services [17, 18] is conducted throughout the state in accordance with the unified requirements of the National Health Commission in Liangshan Prefecture. An important part of this work is to build an interactive platform for family doctors and contracted residents, providing services such as appointments, consultation, health management, and follow-up visits for NCDs. Regularly and accurately push health education information according to different service needs, seasonal characteristics and epidemic situation [19, 20]. Therefore, taking advantage of the Family Branch System and Contracted Family Doctor Services in Liangshan Prefecture is expected to be key in improving the residents’ health literacy.

To this end, this study intends to learn from the experience of AIDS management in Liangshan Prefecture, and proposes an intervention model of health education based on Family Branch System and Contracted Family Doctor Services, which is a Family-based Improvement for Health Literacy among the Yi nationality (FAMILY) in Liangshan, when improving the traditional ICCC framework by strengthen the connection of the three elements at micro level.

Finally, to evaluate the effect of intervention measures while achieving full coverage of beneficial measures, we will adopt stepped wedge cluster randomized trial (SW-CRT), which is widely used in health education, medical staff training and other trial with interventions that benefits outweigh the disadvantages [21–24]. SW-CRT usually has no special control groups, and as the trial goes on, each group will accept intervention sequentially by random, alleviating ethical and moral problems to a large extent when saving resources [25]. Besides, due to the large local population prevalence in Liangshan Prefecture such as migrant workers, etc., some of the study subjects may be lost to follow-up with others may join in the middle process of the study. In view of the above, an open cohort SW-CRT is used in this study [26], with specific study design showed below.

## Methods

### Aims

#### Primary study aim

Propose a set of health literacy intervention mode for the Yi nationality residents in Liangshan Prefecture to improve the health literacy, based on the family.

#### Secondary study aim

Improve the statistical analysis method of SW-CRT, and propose a hybrid model-based main hierarchical causal inference method to solve the common non-compliance problems in SW-CRT.

### Design

This manuscript adheres to the Extensions of the CONSORT Statement and SPIRIT Statement (Additional files 1 and 2).

#### Open cohort stepped wedge cluster randomized trial design

For this study, *N* family branches in the Meigu and Yanyuan County will be included. Each family branch is regarded as a cluster, and *A* clusters constitute a group. It is assumed that there are *N* / *A* groups in the study, the first and third groups are in Meigu County and the second and fourth groups are in Yanyuan County. The experimental study period of the whole project is 1 year, from May 2022 to May 2023. All groups are in non-intervention during the first 3 months (Phase1) of the project. In the second 3 months (Phase2), groups 1 and 2 will start to receive intervention. Then 3 months later (Phase3), groups 3 and 4 will begin to receive intervention. According to the research proposal, all groups will continue to increase 3-month follow-up (Phase4), after all of them having received intervention in a random order, ensuring that study outcomes can be observed when time lag effect of intervention exists (Fig. 1).

**Fig. 1 Fig1:**
[figure not shown]
Stepped wedge study design

#### Study site

The trial is set in Meigu County and Yanyuan County, Liangshan Prefecture, Sichuan Province, China, where have complex and changeable landforms [27]. Meigu and Yanyuan are far apart in geographical location. Specifically, many villages are still dominated by winding mountain highway, and some villages even have no pass roads. The family branches are in a relatively closed state with less communication, which could be helpful to prevent the contamination between the intervention and non-intervention family branches. In addition to the geographical advantage, Meigu and Yanyuan County have also carried AIDS management work, providing practical conditions for the experiment [28, 29].

#### Study object

The project is based on the community health service centres and related medical institutions [30] in the selected districts. Residents will be included if they met all conditions: (1) 15–64 years old, (2) Yi nationality residents living in compact communities, (3) have been living in the district for more than 6 months, (4) native place is Liangshan Prefecture, (5) voluntarily participate in the project and willing to provide informed consent.

People who do not agree to participate and who are unable to participate (such as minors, dementia, schizophrenia and so on) will be excluded.

#### Intervention

The intervention is health literacy education, including project preparation, core group building, promotion within family branch and competition between family branches (Fig. 2), and details are as follows.

**Fig. 2 Fig2:**
[figure not shown]
Intervention strategy

##### Step 0. Project preparation

Organize experts to prepare health literacy knowledge brochures and make operating manuals and activity calendars with reference to the *66 Articles of Health Literacy for Chinese Citizens* [31, 32]. The experts include the experts of health education and NCDs prevention and control from Sichuan University, the experts from Sichuan Center for Disease Control and Prevention (CDC), the head of Health Education Institute and the hard-core of Chronic Infectious Disease Prevention and Control Institute in Liangshan CDC, the director of Health Committee of Liangshan, an expert in the Communication and Health Promotion Department and an expert in Disease Prevention and Control Department in Health Committee of Liangshan, the directors and deputy directors of Meigu CDC and Yanyuan CDC, and an expert from Xichang Community Health Service Center. According to the health literacy knowledge brochures, we produce publicity materials such as towels, umbrellas, and cell phone charging cables based on health knowledge.

The above experts are organized to establish an advisory committee to provide supports including health knowledge, health skills, information technology, and financial to each family branch sponsor, etc.

##### Step 1. Core group building

The sponsors from various branches are recruited by township hospitals, and written and interview examinations are conducted by the advisory committees. This project will train sponsors, including health literacy related knowledge and group promotion training. Moreover, we will provide the sponsors with operating manuals, activity calendars, publicity materials, health literacy knowledge brochures, etc.

##### Step 2. Promotion within family branch

The sponsor of each famliy branch will use the health literacy knowledge brochures to educate other members in famliy branches on health literacy according to the operating manual. We encourage all members of famliy branches to participate in the project, identify problems, propose and implement solutions, conduct self-evaluation and measure improvement. Besides, we require each famliy branch to hold at least one collective sharing meeting monthly.

In terms of nutrition education, we will design and produce nutrition education playing cards in the form of popular 4 or 6 sentences, which are repeatedly revised and proven by a number of nutrition experts. The contents mainly include Chinese dietary guidelines and balanced diet pagoda, the function of nutrients and their main food sources, the nutritional value of various foods, dietary guidance for specific populations and patients with common NCDs, aerobic exercise, weight evaluation and its impact on health, food safety problems, the harm of excessive smoking and drinking, etc. The nutrition education methods will include the following: (1) Distribute nutrition education cards, introducing their main contents and carrying out a quiz on the contents of the cards. Train the sponsors to explain the cards to other family members through their publicity. (2) Distribute nutrition health knowledge publicity materials, and ask the use of the cards to supervise. (3) Set up nutrition knowledge bulletin boards and post nutrition health knowledge bulletin materials. (4) Start nutrition knowledge courses and lectures. (5) Set up personalized online or offline nutrition counseling and guidance stations which are mainly based on the actual dietary situation of the residents, and provide relevant dietary nutrition guidance after analysis.

We will organize training and seminars for the members of the advisory committee, the heads of project health center, and the sponsors of each family branch. In the meetings, each family branch sponsor needs to give feedback on the problems encountered in the intervention implementation process, and the committee members will make suggestions in response to the problems. We will train the sponsors on health literacy knowledge and distribute the publicity materials. Besides, the family branches are encouraged to exchange learning experiences. Regularly invite leaders of the Liangshan Prefecture Health Committee to attend the meeting to report on the interventions in the recent months, and receive advice and guidance.

##### Step 3 competition between family branches

Take advantage of traditional Yi festivals to conduct health literacy knowledge competitions on a regular basis by family branches. We will distribute the prizes according to the competition rankings, and issue the honorary certificates to the family branches with outstanding scores. Use the concept of family honor of Yi nationality to stimulate the internal motivation of residents to improve health literacy, exam and test the actual mastery of health literacy knowledge through competitions and other means.

#### Control

The project uses Contracted Family Doctor Services as a control measure, which is currently an important routine measure to improve residents’ health literacy in Liangshan Prefecture. Therefore, the project takes it as a control measure and compares it with the effect of intervention measures.

#### Outcome

The primary outcome of the project is the health literacy level of residents in the *Health Liangshan Yi Autonomous Prefecture Performance Evaluation Index*, which is defined by the 2020 *Residents Health Literacy Monitoring Questionnaire* [33].

The secondary outcomes are prevalence of hypertension, prevalence of diabetes, BMI, smoking intensity index [34], and alcohol consumption [35]. The project will measure the outcome indicators at 1, 3, 6, 9, and 12 months.

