**Fig. 3 Fig3:**
[figure not shown]
SPIRT Figure

Data collectors will also collect information on smoking and alcohol consumption, and measure participants’ height, weight, blood pressure, and blood sugar. The sponsor of family branch will inform the participants of the time and place of measurement, and the need to fast for one night. All participants will be informed of the study information orally and in writing, prior to the questionnaire and physical examination, and their data will be collected only after providing written informed consent.

Data collection will follow standard data management protocols. The research will provide suitable survey sites, and assign special personnel to be responsible for on-site supervision, double data entry, data coding, data verification, and data preservation. Only members of the research team have access to the data, and identifiable data will not be collected and will be replaced by serial numbers to reduce the risk of privacy disclosure, so there will be no risk to residents’ privacy.

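### Hypertension and diabetes enter the secondary outcomes only as prevalence, although the blood pressure and fasting blood sugar already measured at every round would be more sensitive outcomes

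*Protocol article*

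**What the plan says.** The Outcome section makes health literacy the primary outcome and names five secondary outcomes. Three of them read: "The secondary outcomes are prevalence of hypertension, prevalence of diabetes, BMI". The other two concern smoking and drinking. On timing: "The project will measure the outcome indicators at 1, 3, 6, 9, and 12 months".

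The Data collection section puts a physical examination at each of those rounds. Collectors record "height, weight, blood pressure, and blood sugar", and participants are told of "the need to fast for one night". So BMI is used as a continuous outcome, while the blood pressure and fasting blood sugar from the same visits appear among the outcomes only through the two prevalences.

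The Intervention section states: "The intervention is health literacy education". The design section gives 3-month phases with two crossover points. The first is worded: "In the second 3 months (Phase2), groups 1 and 2 will start to receive intervention". The remaining two groups cross over one phase after that. The first phase has no treated branch, and after the second crossover no control branch remains. A further 3-month phase allows for a delayed effect, but every branch is then treated.

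The article does not say how a case of hypertension or diabetes is determined. That alone is not a finding, since a condensed article can leave case definitions to the full protocol.

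**The concern.** An education programme can be expected to shift blood pressure or glucose modestly across many people. A yes/no state registers only those who cross a threshold and ignores movement on either side of it. The randomised side-by-side contrast lasts 3 months, and the longest exposure of any branch is 9 months, so a large change in prevalence would be needed quickly.

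At stake is how two of the five secondary results will be read. With low power, a null result for prevalence is likely even if the programme shifts the underlying values. A reader could then take it as evidence that better health literacy does nothing for blood pressure or glucose, although more informative data had been collected at the same visits.

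**Working it through.** **The plan's own figure.** The article gives no power statement for the prevalence outcomes. Its only figure, 7.699 clusters, is for the primary outcome. The variance formula below, with the primary inputs and two crossover points, gives a total of about 30.4 to 30.8 clusters. A quarter of that is 7.59 to 7.70, so 7.699 is matched as a number per group of four but not as the total the article calls it. That is a separate matter; here the match only supports use of the formula.

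**Inputs from Sample size and sampling method.** 12 branches, 50 people per branch and round, cluster autocorrelation 0.9, individual autocorrelation 0.7, retention 0.6, two-sided alpha 0.05 (sidedness assumed). The plan's ICC of 0.4 was set for the primary outcome.

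**Assumed, not in the documents.** Prevalence 10% to 30% (20% for power), ICC 0.01 and 0.05 alongside 0.4, a shift of 0.2 SD, normal values, and prevalence defined by a cut of the current reading.

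**Step 1: information kept by the cut**, φ(z_p)² / [p(1−p)]:
- p = 0.10: 0.1755² / 0.09 = 0.34
- p = 0.20: 0.2800² / 0.16 = 0.49
- p = 0.30: 0.3477² / 0.21 = 0.58

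**Step 2: standard error of the effect.** Generalised least squares on branch-by-round means with fixed round effects. The covariance between rounds d apart is ICC × 0.9^d + (1−ICC)/50 × 0.6 × 0.7^d in SD units, with the factor 0.6 dropped at d = 0. The rounds at months 1 and 3 are untreated; at month 6 half the branches are treated; at months 9 and 12 all are. The SE per SD is 0.0717, 0.0807 and 0.1310 at ICC 0.01, 0.05 and 0.4.

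**Step 3: detectable change at 20% prevalence.** The SD of a yes/no value is √(0.2 × 0.8) = 0.4, and the multiplier is 1.96 + 0.84 = 2.80.
- ICC 0.01: 2.80 × 0.4 × 0.0717 = 8.0 points
- ICC 0.05: 2.80 × 0.4 × 0.0807 = 9.0 points
- ICC 0.4: 2.80 × 0.4 × 0.1310 = 14.7 points

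These are falls of 40% (8.0/20) to 73% (14.7/20) of all cases. At 10% prevalence and ICC 0.4 the change needed is 2.80 × 0.3 × 0.1310 = 11.0 points, more than exists. Four periods instead of five rounds, or geometric retention, changes the results at 20% by at most 0.1 point.

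**Step 4: the binary ICC.** Cutting a value lowers its ICC. A latent 0.4 becomes about 0.23 at 20% prevalence, and the detectable change drops from 14.7 to about 12.2 points.

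**Step 5: power for a 0.2 SD shift.** A 20% prevalence moves to Φ(−0.842 − 0.2) = 14.9%, a fall of 5.1 points.
- ICC 0.01, mean: Φ(0.2/0.0717 − 1.96) = Φ(0.83) = 80%. Prevalence: Φ(0.0512/0.0287 − 1.96) = Φ(−0.17) = 43%, or 44% with the lowered binary ICC.
- ICC 0.05: 70% against 35% (same ICC for both).
- ICC 0.4, mean: Φ(0.2/0.1310 − 1.96) = Φ(−0.43) = 33%. Prevalence: Φ(0.0512/0.0524 − 1.96) = Φ(−0.98) = 16%, or 21% with the lowered binary ICC.

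**The case against.** The strongest reply is that reduced power is not inability. A reader might infer that prevalence cannot show a benefit, or must come out null, because these are chronic states that hardly reverse in 3 months. The documents do not support that. They describe only measured readings, under which prevalence can fall, and they give no reversal rate. The calculation above still leaves prevalence 43–44% power in the favourable case.

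A reader might also infer that repeated screening would push prevalence up and make the programme look harmful. All branches are measured at the same rounds, and the mixed model has a fixed effect for each stage, so a rise common to all branches is absorbed there. Only extra detection caused by the education itself could distort the contrast, and only if known diagnoses count as cases. In that case prevalence would also respond less. The article does not say, so this remains a possibility.

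Three further points stand. At the plan's ICC the mean is weak too (33%). A more stable individual state would help prevalence somewhat: individual autocorrelation 0.95 at ICC 0.01 gives 7.0 rather than 8.0 points. And the stated aim is health literacy, with these two among five secondary outcomes in a trial its authors call exploratory, so the weight is moderate. None of this removes the mean's advantage at every ICC tried.

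**Conclusion.** The point holds as a matter of sensitivity. Listing hypertension and diabetes only as prevalence leaves the more informative measurements from the same visits outside the outcome list. On a current-reading definition, prevalence keeps about a third to just under three fifths of the information. At 20% prevalence it needs a fall of about 8 to 15 points for 80% power (about 12 points at a latent ICC of 0.4 once the binary ICC is lowered). For a 0.2 SD shift, the mean has about 1.5 to 2 times the power of prevalence.

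The figures rest on assumed prevalence, effect size and ICCs other than 0.4, on normal values, and on the current-reading definition. They do not show that the prevalence outcomes are bound to fail or to mislead in direction. Nor do they require prevalence to be reduced to baseline description.

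**What to change.** Add mean systolic blood pressure, mean diastolic blood pressure and mean fasting glucose as secondary outcomes, analysed with the same mixed model as BMI. State that conclusions about an intervention effect on blood pressure and glucose rest mainly on these. Prevalence of hypertension and of diabetes may stay listed as supportive outcomes, with a sentence that a null result there is not evidence of no effect.

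No new visit or measurement is needed. The Study status section says recruitment was still being prepared at publication, and it already provides for protocol changes to be recorded in the registry. The cost is two or three more secondary analyses. Means are also affected by changes in drug treatment during the trial, so use of such drugs should be recorded in the existing questionnaire and taken into account in interpretation.
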